## Study design

## Open label, multicenter, double-arm interventional randomized phase I/II clinical trial study.

This Phase I/II escalating-dose clinical trial is a randomized study to determine RP2D, safety, tolerability, alloreactivity and efficacy of cell therapy with allogeneic NK cells (arm A) and T memory cells (arm B) from blood donors who have recovered from COVID-19 and are currently disease-free.

Donors and patients will be HLA tested and allocated into two different arms:

- **Arm A**: If one or more HLA class I match between donor and recipient are present, patients will receive memory T cells.
- **Arm B**: If donor and recipient have less than 1 HLA class I match or HLA-KIR mismatch, they will receive NK cells.

There will be two consecutive phases in the study:

1. The first dose escalation segment focuses on determining safety and the recommended dose for the second segment.
2. Phase II focuses on efficacy and safety.

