## Subject Treatment Assignment

Patients will be allocated into two groups: Arm A and Arm B depending on HLA typing.

For the phase I, patients on each arm will subsequently undergo a correlative allocation into the different cohorts (1,2,3).

The decision to proceed to each subsequent dose level (next cohort) will be made based on safety and tolerability data from the prior lower dose level. Safety data for at least 7 days post-dose from all the subjects at the prior lower dose will be reviewed before dose escalation.

The next cohort will open if all the patients in the previous cohort have been included and no safety issues have aroused during the follow-up after cell infusion (data of at least 7 days after cell infusion is required to proceed to each subsequent dose). Patients will continue to be followed for possible DLTs during the 21 days following cell infusion.

For phase II, eligible patients will be allocated to arm A or B considering HLA typing and within each arm they will then be randomized in a 1:1 ratio to 1 of 2 treatment groups (SoC or SoC+RP2D).

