## Additional Assessments

## Will be performed as far as possible considering the increased work-load and if the investigator considers it appropriate:

- SARS-CoV-2 testing by PCR: Days 7, 14, 21, 28 and 90 or until a negative result is obtained, whichever occurs first.
- Blood samples for:
- Hematology and Chemistry: Day 3, 7, 14, 21, 28.

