# Markers of Immunological function: Performed weekly.

- Donor chimerism: Day 3 and 7. If donor chimerism persists by day 7, repeat, 14, 21, 28 or until disappearance (weekly until disappearance).

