## Follow-up

Patients will be followed up until day 90, discharge or death, whichever occurs earlier. However, if the patient is discharged before day 30, weekly ambulatory visits (days 7, 14, 21 and 28) will be performed if the investigator considers it appropriate.

Donor chimerism will be evaluated on days specified in the schedule of assessments and weekly until disappearance in all patients.

If the patient has been discharged before day 30 they will be contacted by phone at Day 30 and Day 90 to obtain information about evolution and adverse events.

Patients discharged after day 30 will be contacted by phone at Day 90 to obtain information about evolution and adverse events.

**End of study:** The end of study date will be the date of the last visit of the last patient included.

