## INFORMATION ON ADVERSE EVENTS

The investigator will monitor and systematically collect the AEs starting from the signing of the Informed Consent Form until the final follow-up visit of each subject.

The occurrence of AEs must be sought by non-directive questioning of the subject at each visit during the study. Adverse events may also be detected through physical examination findings, laboratory test findings, or other assessments.

Also, the investigator will assess and record, in detail, the AE, including the start and end dates, the description of the event, severity, course, outcome, the relationship of the AE with the investigational medicinal product and the measures taken (treatments, additional complementary examinations, etc.).

The AE will be recorded in the medical history and recorded in the Case Report Form.

The subjects who present with an AE will be subjected to relevant follow-up until its resolution or until it is judged to be permanent. The type of follow-up will be conducted according to the relevant criteria depending on the particular event.

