# General considerations

Tabular summaries will be presented by treatment group.

Categorical data will be summarized by number and percentages. Continuous variables will be summarized by descriptive statistics. Recover incidence (RI): Time to recovery.

The overall survival rate will be calculated by the nonparametric Kaplan-Meier method. Fisher exact test will be used to identify those patient characteristics that are significantly associated with treatment response (complete or partial).

For quantitative characteristics a chi-squared trend test will be conducted to examine whether the proportion of patients responding to treatment either increased or decreased across the levels of the characteristic.

The results of the statistical analysis will be displayed in the tables and as mean ± SD in the Figures. Levels of significance will be expressed as p-values (*p < 0.05).

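### Post-discharge adverse-event contacts are not fixed alike for the two Phase II groups: donor chimerism testing, on which the protocol contradicts itself, may give some infused patients extra enquiries

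*Protocol*

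**What the plan says.** Phase II randomises patients 1:1 within each HLA-defined arm to standard of care (SoC) alone or SoC plus cells, open label (Study design; Subject Treatment Assignment).

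Until discharge, adverse events (AEs) are reviewed daily in every patient (Daily Study Assessments). After discharge, four places in the protocol matter:

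- **Follow-up, visits.** For a patient discharged before Day 30, "weekly ambulatory visits (days 7, 14, 21 and 28) will be performed if the investigator considers it appropriate".
- **Follow-up, chimerism.** "Donor chimerism will be evaluated on days specified in the schedule of assessments and weekly until disappearance in all patients".
- **Follow-up, telephone.** Patients discharged before Day 30 are called on Days 30 and 90, and those discharged later on Day 90 only. The calls cover AEs and apply to both groups.
- **Additional Assessments.** The whole list, chimerism included, carries the condition "Will be performed as far as possible considering the increased work-load and if the investigator considers it appropriate". The chimerism entry tests on Days 3 and 7 and continues only if the Day 7 result is still positive. The Phase II schedule (Table 3) says the same and stops testing once the result is negative.

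On how AEs are found, Information on Adverse Events says: "The occurrence of AEs must be sought by non-directive questioning of the subject at each visit during the study". On reporting, General considerations says: "Tabular summaries will be presented by treatment group".

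**The concern.** Because AEs are asked about at each visit, any extra visit is an extra AE enquiry. After discharge the protocol gives infused patients a reason to come back that SoC patients cannot have, since SoC patients have no donor. The remaining visits are left to an investigator who knows the allocation.

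If contact differs by group, part of any excess of mild or moderate AEs in the cell group could come from more frequent asking. The data would not allow that part to be separated from harm by the cells. The secondary safety outcome is also exposed: it counts treatment-related AEs, and the protocol's definition of a related event can be met by a temporal relationship alone. An event picked up at a chimerism visit could enter that outcome directly. No later analysis can restore contacts that were never made, so the schedule has to be settled in the protocol.

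**Working it through.** The plan states no figure on this point, so the check is a count of post-discharge AE contacts under the protocol's own rules.

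**Inputs from the protocol**
- Calls on Days 30 and 90 in both groups if discharge is before Day 30.
- Optional visits on Days 7, 14, 21 and 28.
- Chimerism on Days 3 and 7, then weekly while positive.

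**Assumptions**
- A return for the chimerism sample counts as a visit.
- The Day 7 test is done in every infused patient.
- SoC patients are not tested.
- The day of discharge and the day of the first negative result are illustrative, because the protocol gives neither.

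**Formula**
- SoC contacts = 2 calls + optional visits held.
- Cell contacts = 2 calls + chimerism days after discharge, up to and including the first negative + any other optional visits held.

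Example, discharge Day 10, first negative Day 21, no optional visits: 2 + 2 (Days 14 and 21) = 4. If positive through Day 84, the weekly days from 14 to 84 number (84 − 14)/7 + 1 = 11, so 2 + 11 = 13.

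*Reading A: the chimerism sentence in Follow-up is binding.*

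| Discharge | Chimerism first negative | No optional visits: SoC / cell | All optional visits: SoC / cell |
|---|---|---|---|
| Day 5 | by Day 7 | 2 / 3 | 6 / 6 |
| Day 5 | Day 14 | 2 / 4 | 6 / 6 |
| Day 5 | positive through Day 84 | 2 / 14 | 6 / 14 |
| Day 10 | by Day 7 | 2 / 2 | 5 / 5 |
| Day 10 | Day 14 | 2 / 3 | 5 / 5 |
| Day 10 | Day 21 | 2 / 4 | 5 / 5 |
| Day 10 | Day 28 | 2 / 5 | 5 / 5 |
| Day 10 | positive through Day 84 | 2 / 13 | 5 / 13 |

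*Reading B: the condition in Additional Assessments governs.* No chimerism visit is compulsory, and the required contacts are 2 / 2 in every row. The visits actually held then depend on the investigator.

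**Limit on the effect for a patient discharged on Day 10.** The part of the first 30 days that an SoC patient without optional visits covers only by recall at the Day 30 call is (30 − 10)/30 = 67%. Suppose non-serious events are spread evenly over the 30 days and recall misses 20% to 50% of them. Both are assumptions with no source in the protocol. The loss is then 0.67 × 0.20 = 13% to 0.67 × 0.50 = 33% of events.

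That is a loss within the SoC group, not a between-group difference. It would equal the difference only if infused patients lost nothing. An infused patient discharged on Day 10 and negative by Day 7 has the same two calls and the same loss, so the difference is zero.

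**The case against.** The strongest case against rests on four points.

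- **Nothing compels infused patients to return.** Chimerism stands in a list that is discretionary as a whole. This is right as far as it goes, and a reader who inferred from Follow-up alone that infused patients must come back would be going too far. What remains is a conflict between two sections. Under the discretionary reading, 2 against 2 is the minimum number of contacts and does not show that actual contacts are equal. An investigator who knows the allocation has a chimerism reason to recall infused patients only.
- **SoC patients are scheduled too.** Table 3 lists examination, vital signs, PCR and immune markers on Days 7, 14, 21, 28 and 90 for all Phase II patients, and recovery on Day 14. The optional visits and the calls are worded alike for both groups. So it would be wrong to infer that SoC patients are contacted only if the investigator wishes. If every optional visit is held, the groups are equal through Day 28. But Follow-up is the section that says what happens after discharge, and it makes these visits optional.
- **The asymmetry is inferred.** Follow-up says all patients, and Table 3 does not limit the chimerism row to infused patients. That is true. Read literally, however, it orders a donor test in patients without a donor, so the text needs correcting on that ground as well.
- **The affected comparison is narrow.** The AE outcome is descriptive and concerns treatment-related events, no between-group AE test is specified, and a chimerism sample is not a haematology or chemistry panel. This lowers the stakes. Tables by treatment group will still be read side by side.

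**Conclusion.** The point holds as a risk built into the contact schedule. The protocol does not fix the same post-discharge AE contacts for the two Phase II groups, and it contradicts itself on whether chimerism testing is discretionary. Infused patients may have more AE enquiries if they are discharged before the Day 7 test or if chimerism persists after it.

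The size is unknown and may be nil. It depends on chimerism persistence, the timing of discharge and how many optional visits are held, none of which the protocol gives. The counts range from no difference to 2 against 14 contacts in the extreme illustrative case. The 13% to 33% figure rests on assumed recall loss and is at most an upper bound on the difference for discharge on Day 10.

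A reader might infer that AEs are in fact sought more often in the cell group. The documents do not support that. They show only that it can happen, for some infused patients, under one of two conflicting sections.

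**What to change.** - Amend Follow-up to set one AE contact schedule for both Phase II groups whatever the chimerism result: Days 7, 14, 21, 28 and 90, by visit or, for discharged patients, by telephone with the same non-directive questions.
- Reconcile Follow-up with Additional Assessments on whether chimerism testing is discretionary, and state in Follow-up and Table 3 that it applies to infused patients only.
- Record on the case report form the contact at which each AE was found, so that events first found at extra chimerism visits can be shown separately.

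The choice of a main harm comparison, such as serious or grade 3 and higher events, can be left to the SAP and is not part of this request.

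The cost is up to four short calls per discharged patient (Days 7, 14, 21 and 28, as the Day 90 call already exists), one case report form field and the amended text. No new clinical procedure is needed.

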1. STUDY OUTCOME MEASURES

## Primary outcome:

**Phase I**

The primary outcomes of the Phase I in this study are:

- The primary outcome will be the occurrence of DLTs in all patients during the study treatment, until 21 days after cell infusion, and the MTD.

DLT is defined as:

- - any grade 3 or higher toxicity with an attribution of definitely or probably related to the infusion of the cells and
  - any lower grade toxicity that increases to a grade 3 or higher as a direct result of the cell infusion.

Based on this, **RP2D** will be defined as: The recommended dose will be the MTD unless no MTD is determined in the dose escalation segment of the study. In the latter, the recommended dose will be the highest dose evaluated in the dose escalation segment.

- Incidence and nature of DLT of a single infusion of NK or memory T cells from a healthy donor recovered from COVID-19 (dose escalation).

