## Secondary outcomes:

- Time (days) to normal level of lymphocytes.
- Proportion of patients showing clinical improvement at day 7 according to the investigator (based on respiratory status and blood-result tests).
- Proportion of patients receiving a second cycle.
- Time (days) to first negative SARS-CoV-2 PCR after infusing adoptive NK cells or adoptive memory T cells.
- The incidence of treatment-related adverse events (new or worsening from baseline) will be summarized by system organ class and/or preferred term, severity, type of adverse event and relation to study treatment. They will be defined by the Common Terminology Criteria for Adverse Events (CTCAE) Version 5.0
- Duration (days) of hospitalization.
- Time (days) to discharge or to a NEWS (Appendix 1) of ≤ 2 and maintained for 24 hours, whichever comes first.
- Time to improvement by one category on a 7-point ordinal scale (Appendix 2).
- Subject clinical status (on a 7-point ordinal scale) at day 14.
- Proportion of patients requiring intensive care unit.
- All-cause mortality at Day 28.

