**Relationship to Study INTERVENTION**

All adverse events (AEs) must have their relationship to study intervention assessed by the clinician who examines and evaluates the participant based on temporal relationship and his/her clinical judgment. The degree of certainty about causality will be graded using the categories below. In a clinical trial, the study product must always be suspected.

- **Related** – The AE is known to occur with the study intervention, there is a reasonable possibility that the study intervention caused the AE, or there is a temporal relationship between the study intervention and event. Reasonable possibility means that there is evidence to suggest a causal relationship between the study intervention and the AE.
- **Not Related** – There is not a reasonable possibility that the administration of the study intervention caused the event, there is no temporal relationship between the study intervention and event onset, or an alternate etiology has been established.

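### The DLT definition and the causality scale use different terms, and the only adverse-event outcome is limited to treatment-related events, so it cannot compare adverse events between cells and standard of care

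*Protocol*

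**What the plan says.** **DLT.** The Primary outcome section for Phase I makes DLTs up to 21 days after infusion, together with the maximum tolerated dose (MTD), the primary outcome. The first limb of the definition is "any grade 3 or higher toxicity with an attribution of definitely or probably related to the infusion of the cells". The second is "any lower grade toxicity that increases to a grade 3 or higher as a direct result of the cell infusion". The recommended Phase II dose follows from this: "The recommended dose will be the MTD unless no MTD is determined in the dose escalation segment of the study"; otherwise it is the highest dose evaluated. The section on administration dose and schedule says that safety and DLT data from Phase I guide the Phase II dose.

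**Causality.** The section Relationship to Study Intervention says: "The degree of certainty about causality will be graded using the categories below". Two categories follow. *Related* can be met in three ways, the last being "or there is a temporal relationship between the study intervention and event". *Not Related* can also be met in three ways: "There is not a reasonable possibility that the administration of the study intervention caused the event", or no temporal relationship, or another cause established. The section adds: "In a clinical trial, the study product must always be suspected".

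**AE outcome.** The Secondary outcomes section says: "The incidence of treatment-related adverse events (new or worsening from baseline) will be summarized by system organ class". The same sentence goes on to list severity, type of event and relation to study treatment as further ways to split the summary.

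**Setting.** Study design describes an open-label trial whose second phase focuses on efficacy and safety. Subject Treatment Assignment randomises Phase II patients 1:1, within each arm, to SoC or to SoC plus cells.

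**The concern.** There are two separate problems, both about attribution.

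The first is in Phase I. Its primary outcome uses a graded certainty of causation, with *probably* as the lowest grade that counts. The protocol's own scale has no grades of certainty. If investigators have to translate from one to the other case by case, the DLT count depends on the translator. Each cohort has only 3 patients, so one reclassified event changes what the cohort shows. The case most likely to be disputed is foreseeable: the section on risks to recipients names worsening of respiratory distress as a possible infusion reaction, and COVID-19 itself can produce the same picture.

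The second is in Phase II. An outcome restricted to treatment-related events has no natural meaning for patients who receive no cells. In the cell group it rests on judgement by investigators who know the treatment. A randomised control group allows AE rates to be compared without any attribution, and the stated outcome does not use that.

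**Working it through.** The protocol gives no figure for this point, so the check is a comparison of texts plus one count.

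**1. Do the DLT terms exist on the causality scale?**

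- DLT, first limb: definitely or probably related.
- DLT, second limb: direct result of the infusion.
- Recorded scale: *Related* or *Not Related*.

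Neither DLT term is a category of the scale, and no mapping rule is given. An event whose link to the cells is a reasonable possibility, but not a probable one, is *Related* on the scale. Read literally, it falls short of the first DLT limb. The scale does not separate it from a probable or definite event.

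**2. Are the two categories exclusive?** Take a grade 3 worsening of respiratory distress two days after infusion, in a patient whose COVID-19 pneumonia is progressing.

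- Temporal relationship present: it meets *Related*.
- Progressing pneumonia accepted as an established other cause: it meets *Not Related*.

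The criteria within each category are alternatives, so one event can satisfy both. The sentence that the product must always be suspected leans towards *Related*, but it does not say which criterion prevails. The same event is therefore a DLT under one defensible reading and not under another.

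**3. What depends on it?** The chain in the protocol runs from DLTs to the MTD to the recommended Phase II dose, with the highest evaluated dose as the fallback when no MTD is determined. The classification thus bears on the dose carried forward. How strongly cannot be calculated, because the protocol does not state how many DLTs would define an MTD.

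**4. What can the AE outcome show in Phase II?** Phase II has 82 patients in each of arms A and B, so 2 × 82 = 164. With 1:1 randomisation within each arm, 82 / 2 = 41 per arm are planned for SoC alone, or 2 × 41 = 82 in total. These 82 receive no cells, so no event can be related to cells. A between-group comparison of this outcome would not estimate a difference in AE risk.

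**5. Is the AE outcome consistent with itself?** Counting events that are new or worsening from baseline describes treatment-emergent events, whatever their cause. Splitting by relation to treatment is informative only if unrelated events are included. Both features conflict with the restriction to treatment-related events.

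**6. Are the data for a better outcome collected?** Yes. Information on Adverse Events has AEs collected for each subject from consent to the final follow-up visit, with severity and relationship recorded. Nothing is lost at data capture for the all-cause comparison.

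**The case against.** **DLTs have their own assessment.** Table 2 has a DLT row apart from the adverse-events row, and several sections prescribe 21 days of DLT follow-up. The case report form is not shown and may record certainty directly. This stands against the inference that a DLT cannot be derived at all: an investigator may tick it. It does not remove the conflict, because that investigator would still be applying a threshold that the protocol's causality section neither contains nor defines.

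**Other harm outcomes do not depend on attribution.** Day 28 all-cause mortality, need for intensive care and the 7-point scale are defined for everyone, and the general statistical section tabulates by treatment group. A reader might infer that Phase II cannot compare safety; for these outcomes it can. Only the AE outcome is affected.

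**SoC is listed among the randomised treatments.** An event could in principle be related to SoC, so a control count of exactly zero is not certain. That is fair. But such a count would set SoC-related events against cell-related events, which is not a useful comparison. The outcome is also not specific to Phase II, and it raises no comparison problem in uncontrolled Phase I.

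**It is only a slip for treatment-emergent.** That is quite possible, given the rest of the sentence. It still needs correcting, because the outcome is stated in the protocol and as worded excludes the events in question.

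**The statistical analysis plan can settle this.** It can choose tables and effect measures. It cannot recover certainty grades that were not collected, and it should not have to overrule a protocol definition.

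The open-label design is declared and is not itself an error. It is only a further reason not to rest a group comparison on attribution.

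**Conclusion.** Both parts hold, as faults of definition. (a) The DLT wording and the causality scale do not share terms, the two causality categories overlap, and no rule connects them, so classification of the same event can differ for an outcome that guides the Phase II dose. (b) The only AE outcome cannot compare AEs between cells and SoC, with 82 of the 164 planned Phase II patients on SoC alone, and it contradicts its own wording.

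It is tempting to attach a probability that a 3-patient cohort shows a DLT under a broad and under a narrow reading. The documents do not support that. They give no background rate of grade 3 or higher events and no DLT count as a decision threshold; escalation turns on the absence of safety issues with at least 7 days of data. The size of (a) therefore stays qualitative. The conclusion assumes that the causality section is the scale actually used on the case report form. If the form already records certainty grades, (a) reduces to a correction of the protocol text, and (b) is unchanged.

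**What to change.** 1. Reconcile the DLT definition in the Primary outcome section with Relationship to Study Intervention so that both use the same terms. Either the recorded categories carry the certainty grades that the DLT definition needs, or the DLT definition refers to the recorded categories. State which category prevails when an event meets both. The threshold is a clinical decision for the sponsor.
2. In Secondary outcomes, define the AE outcome as all new or worsening AEs regardless of attribution. In Phase II, count them in both randomised groups from one common start point, randomisation, since SoC patients have no infusion date.
3. Compare grade 3 or higher AEs and serious AEs between the groups. Keep related events as a descriptive table for the cell-treated patients.

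The cost is revised wording in three sections, one more table, and possibly one extra field on the case report form if certainty grades are to be recorded. No additional AE collection is needed for the group comparison.
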